
### Data and safety monitoring

The Data and Safety Monitoring Plan will align with the MSK DSM Plan where possible: https://one.mskcc.org/sites/pub/clinresearch/Documents/MSKCC%20Data%20and%20Safety%20Monitoring%20Plans.pdf and MSK’s Data Safety and Monitoring Committee (DSMC) will have oversight of the trial, including protocol monitoring, compliance, and data verification audits, staff education on clinical research quality assurance. The DSMC will initiate review following the enrollment of the first participant, or by the end of year one if no accruals, and will continue for the study lifecycle until there are no participants under active therapy and the protocol has closed to accrual.

### Adverse reactions and events

Participants may find some questions in the psychosocial assessments upsetting. However, as measures were chosen to reflect what are likely to be existing concerns, the present study is not expected to markedly increase participants’ psychological distress above their routine concerns. Topics covered during MCP-Ch sessions may be emotional, but related distress is expected to be transient and will be supported by a mental health clinician. In addition, experienced research staff trained in interviewing medically ill individuals will administer all study measures and will be supervised by the study principal investigators (PIs). If a participant wishes to stop participating in the study for any reason, we will request that they inform the research team and, if willing and able, their reason for ceasing participation. If a participant appears to be at risk for harming himself/herself or others during the course of the trial, the researchers will take immediate action to address this risk and the participant would become ineligible for continuing with the study.

Potential adverse events for this trial are expected to be non-physical in nature. The principal investigators will report unanticipated and serious adverse events to the IRB in a timely manner on an ongoing basis. For the purposes of this study, a serious adverse event is defined as an event that, as a direct result of the study, causes serious harm (e.g., death or serious injury) to the participant. Adverse events are also reported as part of the progress reports submitted to the National Institutes of Health. If at any point during the study period the intervention is found to be associated with an undue risk of harm to participants, then the trial will be stopped—such as if the research team determines, in good faith, that the intervention appears to be causing significant emotional distress or impairment for participants beyond what would be expected or leading to increased risk for harm to self or others.

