### Assignment of interventions

Participants will be registered by the MSK institution-wide, central Protocol Participant Registration system and randomized (using the Clinical Research Database) to receive MCP-Ch with equal probability via (1) an English-speaking interventionist and an RSMI interpreter; (2) an English-speaking interventionist and an RCMI interpreter; or (3) a bilingual Mandarin-speaking interventionist (no interpreter). Research assistants will randomize a participant following the participant’s completion of the consent, eligibility screener, and baseline assessment. Because a PI ([name]) will be conducting supervision for the interventionists, and because different assessments will be administered depending on the intervention assignment (e.g., clinically significant interpreting errors will be assessed only in the RCMI and RSMI arms), the only person completely blinded to group assignment will be the data analyst/statistician.

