## Outcomes

The first goal of INTERPRET-PSY is to determine the feasibility of using RSMI and RCMI to deliver a manualized, culturally adapted counseling intervention to LEP cancer patients. Participants will be deemed not evaluable for feasibility if they drop out prior to Session 6 due to non-intervention related issues (e.g., progression of cancer or death). These non-evaluable participants will be replaced and reasons for dropout tracked. A determination of feasibility for RSMI/RCMI (*primary outcome*) will be met if *n* = 11 complete treatment (a comparable 67% MCP completion rate was achieved in [name] original MCP trial [35]), defined as completing 5 out of 6 sessions (i.e., ≥11 out of 15 participants completing ≥5/6 sessions). We will also calculate the observed recruitment rate, retention rate, participant satisfaction with treatment protocol (*secondary outcome*, scored by calculating the percentage of positive “agree” responses on a satisfaction survey), and telehealth usability in all 3 arms (RSMI, RCMI, bilingual provider). These outcomes will be measured quantitatively within 1 month following the intervention (T8) through a post-intervention assessment.INTERPRET-PSY also will assess the effect of interpreter-mediated delivery on counseling/psychotherapy process outcomes. This will be measured by comparing the RSMI and RCMI groups to the “gold standard” bilingual provider group at post-intervention assessment (T8), administered within 1 month following the intervention. Outcomes will include therapeutic alliance, MCP-Ch content comprehension, and the number and nature of clinically significant interpreting errors in MCP-Ch Session 1 (*secondary outcomes*); participants’ treatment expectancy, post MCP-Ch session 1 (T2); and distress, spiritual well-being, quality of life, anxiety and depression, meaning in life, and hopelessness (*exploratory outcomes*). We will also assess post-session ratings after each MCP-Ch session (T2, T3, T4, T5, T6, and T7).We will identify barriers and facilitators to successful interpreter-mediated delivery of MCP-Ch in semi-structured interviews with “extreme responders” in each of the 3 arms (i.e., participants who score especially high or low on therapeutic alliance, MCP-Ch comprehension, and/or acceptability). These will be assessed approximately 3 months post-intervention (T9).

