## Measures

A description of each quantitative measure used at each assessment is provided in Table 2, and a timeline of assessments is provided in Table 3. Most measures have demonstrated good reliability and validity in Mandarin-speaking populations (Table 2). Surveys that do not have validated Chinese translations will be translated and checked for quality by qualified translators using an established five-step process for translation and evaluation developed by Forsyth et al. [39]. All measures will be administered either by phone or videoconference by trained bilingual research staff and entered into REDCap, a secure web platform for electronic data capture.

**Table 2 Tab2:** List of assessments

Measure Title	Time Points Used	Outcome	Description of Measure
Demographic and Clinical Characteristics	T1 (Baseline)	n/a	Age (years), gender, race, ethnicity, education, preferred language, level of English proficiency, country of origin, immigration length, frequency of revisiting birthplace, employment status, household income, marital status, household size, religious/spiritual beliefs, health insurance status, most recent cancer diagnosis, and current cancer treatment received
Digital Health Care Literacy (DHCL) [40]	T1 (Baseline)	n/a	The DHCL is a brief (3-item), face valid measure of one’s confidence in the ability to use technological programs or services and the ability to independently troubleshoot technical issues. Cronbach’s α = 0.90 [36]
Feasibility	T8 (Post-intervention)	Primary	Feasibility will be assessed via attendance logs and defined as ≥11 out of 15 participants completing ≥5/6 sessions
Acceptability	T8 (Post-intervention)	Secondary	A 20-item, investigator-initiated, face-valid survey to assess participants’ satisfaction with the intervention, mode of delivery (via RSMI or bilingual interventionist) and effects of treatment (i.e., whether the intervention was helpful). Acceptability will be scored by calculating the percentage of positive (“agree”) responses
Therapeutic Alliance (WAI-S) [41]	T2, T3, T4, T5, T6, T7 (Post-sessions 1–6)	Secondary	The Working Alliance Inventory-Short Form (WAI-S) is a 12-item self-report scale of therapeutic alliance with 2 forms: one for the client, and one for the interventionist. Cronbach’s α = 0.86. [42]*

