### Post-session assessments (T2, T3, T4, T5, T6, T7)

Therapeutic Alliance (WAI-S) [41], Weekly Session Rating and Telehealth Evaluation

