### Post-intervention assessment (T8) administered within 1-month post-intervention

Distress Thermometer (DT) [44], Spiritual Well-Being (FACIT-Sp) [46], Quality of Life (MQOL) [48], Anxiety and Depression (HADS) [50], Meaning in Life (MLQ) [52], Beck Hopelessness Scale (BHS) [54], Telehealth Usability (TSQ) [56], Acceptability, MCP-Ch Concept Comprehension, and Exit Survey

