### Data analysis plan (by objective)

Counseling completion rates will be calculated; we will treat each interpreting arm (RSMI, RCMI) as a single stage design and will assess each separately for feasibility (*primary outcome*). We will calculate frequencies and percentages to summarize recruitment, randomization, retention, acceptability (*secondary outcome*), and usability across all 3 arms (RSMI, RCMI, and bilingual provider). Based on the calculation outlined by Khan, Sarker, and Hackshaw [58], observing 11 or more successes out of 15 in a given arm would allow us to be sufficiently confident that the population feasibility of the corresponding interpretation mode is 90% against a null of 40%. In our calculations, we have set our statistical power to 90% and our Type I error rate to 0.025 to reduce the chance of false discovery. This provides us with sufficient combined statistical power, assuming the two tests are independent.We will summarize (1) therapeutic alliance scores and MCP-Ch content comprehension at T4 across all 3 arms (RSMI, RCMI, and bilingual provider) and (2) number and nature of clinically significant interpreting errors in MCP-Ch Session 1 across the interpreting arms (RSMI, RCMI) (*secondary outcomes*). We will also summarize treatment credibility/expectancy at T2 and differences in post- vs. pre-intervention distress, spiritual well-being, quality of life, anxiety and depression, meaning-in-life, hopelessness by arm (*exploratory outcomes*). These descriptive summaries by arm will provide preliminary indications of whether delivery of psycho-oncology counseling via RSMI or RCMI may potentially achieve clinically significant benefits, which will aid in the design of, and be further assessed in, a subsequent fully powered trial [29]. We will assess baseline contextual factors at T1 (e.g., digital health care literacy, level of English proficiency) to examine whether therapeutic alliance and MCP-Ch content comprehension scores differ by these variables. We will use an error analysis tool developed by Gany et al. [21] to obtain the number and nature of clinically significant errors in MCP-Ch Session 1. Specifically, a panel of 2–4 psycho-oncology clinicians blinded to the interpreting method (i.e., RSMI or RCMI) will review and code transcripts. They will independently code each script to identify clinically significant content and meet to reconcile any differences in their selection of clinically significant content. Examples of potentially clinically significant content include history of cancer diagnosis, past psychiatric history, MCP-Ch session exercises, and plans for future visits. Once all clinically significant content has been identified, a second blinded panel of 2–4 bilingual coders will independently code clinically significant content to identify interpreting errors, yielding a total count of clinically significant interpreting errors. To ensure rigor, coders on both panels will first separately conduct preliminary analyses on a subset of transcripts using the described protocol. Interrater reliability will be assessed by calculating percent agreement. Consensus meetings will be held to adjudicate disagreements and refine error categories and the analytic approach as needed until strong interrater reliability is reached (i.e., *k* = 0.80), at which point coders will commence coding of the remaining transcripts.To assess our semi-structured interviews with “extreme responders,” we will use thematic content analysis [59] to derive insights directly from participants’ narratives, following established guidelines for conducting rigorous qualitative research [60]. First, coders will each read a subset of interviews and develop codes to characterize responses. Coders will then meet to establish an initial codebook, which will be used to code the remaining interviews. Regular consensus meetings will be held to confirm the reliability of coding. The codebook will be iteratively revised as new codes emerge, and codes will be summarized into themes. Prominent themes will include those observed across the majority of interviews as well as key divergences between sub-groups. Findings will be integrated using NVivo [61], which enables qualitative and quantitative data to be paired by participant and in summary format. The coded qualitative data will be explored in relationship to participant outcomes, baseline characteristics, contextual factors, and study arm to further elucidate barriers and facilitators to the implementation of remote interpreting in the psycho-oncology setting.

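### A stop for risk of harm is worded as leaving the study, not just the counselling, so T8 data are lost for patients likely to score poorly on those measures

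*Protocol article*

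**What the plan says.** Adverse reactions and events tells the researchers to act at once on an apparent risk of harm to self or others, and adds that "the participant would become ineligible for continuing with the study". Protection of human subjects adds escalation to the principal investigators and clinical assessment and care. Neither section mentions study assessments after such a stop.

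The T8 list, due within a month after the intervention, holds the distress, spiritual well-being, quality of life, anxiety and depression, meaning and hopelessness scales, telehealth usability, and "Acceptability, MCP-Ch Concept Comprehension, and Exit Survey". Table 2 grades acceptability and comprehension as secondary. The Data analysis plan summarises "differences in post- vs. pre-intervention distress, spiritual well-being, quality of life, anxiety and depression, meaning-in-life, hopelessness by arm" as exploratory outcomes.

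Other data do not depend on T8. Therapeutic alliance and the "Weekly Session Rating and Telehealth Evaluation" are taken after each session (T2 to T7). For the primary outcome, "Feasibility will be assessed via attendance logs".

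Outcomes makes participants non-evaluable for feasibility "if they drop out prior to Session 6 due to non-intervention related issues", with cancer progression and death as examples. It continues: "These non-evaluable participants will be replaced and reasons for dropout tracked".

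**The concern.** Stopping counselling and stopping observation are different decisions, and the safety sentence makes both at once. The trigger is risk of harm. The scales lost at T8 include hopelessness, depression and distress. The missing values are therefore tied to the outcome: the post-intervention summaries would describe the patients who did not reach a crisis. The Data analysis plan wants those summaries to indicate whether interpreter-mediated counselling might bring clinically significant benefit, as an aid to designing the definitive trial. An arm with such an exit would look slightly better than it was, and the patients whose experience of interpreted counselling in a crisis is most informative would have no acceptability or comprehension score.

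**Working it through.** **1. What an exit costs, by timing**

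- *Before T8:* acceptability, comprehension, usability, the exit survey and all post-intervention psychosocial scores are lost. (Table 2 and the T8 list both place comprehension at T8; the mention of T4 in the Data analysis plan is a separate matter.)
- *After T8:* only a possible T9 interview is lost.
- *Kept in either case:* alliance and session ratings up to the exit, the Session 1 interpreting errors, and the attendance record. Table 2 lists errors and feasibility under T8, but they come from session transcripts and logs, not from a T8 interview.

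**2. Effect on a T8 arm mean**

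Inputs: 15 patients per arm (Trial design); one exit before T8 (assumed, since the article gives no rate); the missing patient's change differs from the mean *m* of the other 14 by *d* SD (assumed, range 1 to 2).

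- Mean of all 15 = (14*m* + *m* + *d*)/15 = *m* + *d*/15.
- The summary reports *m*, so the error is *d*/15.
- *d* = 1: 1/15 = 0.067 SD. *d* = 2: 2/15 = 0.133 SD.
- If the patient is replaced, 16 patients contribute or should have contributed, and the error is *d*/16: 0.063 or 0.125 SD.
- For scale, the standard error of a mean of 14 is 1/√14 = 0.267 SD, so the error is about a quarter to a half of one standard error.
- No exits: zero.

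**3. Side check on the primary outcome**

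The plan's rule reproduces. With 15 patients and a cutoff of 11, the exact binomial chance of passing is 0.0093 at 40% completion and 0.987 at 90%. A cutoff of 10 would give 0.0338 at 40%, above the stated 0.025.

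Missing T8 data do not touch this count. Whether the exit is replaced or kept as a non-completion can. Take one exit before five sessions and 14 other patients who complete with probability *p*. The class of the exit decides between go and amend only if exactly 10 of the 14 complete and the replacement also completes: P(Bin(14, *p*) = 10) × *p*.

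| *p* | P(Bin = 10) | × *p* | Check: P(≥11 of 15) − P(≥11 of 14) |
|---|---|---|---|
| 0.67 (completion rate cited in Outcomes) | 0.2164 | 0.145 | 0.4148 − 0.2699 = 0.145 |
| 0.80 (assumed) | 0.1720 | 0.138 | 0.8358 − 0.6982 = 0.138 |
| 0.90 (design target) | 0.0349 | 0.031 | 0.9873 − 0.9559 = 0.031 |

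These figures assume that the exit has happened and that its class is open to dispute. With assumed exit risks of 1%, 2% and 5% per patient, the chance of exactly one exit in 15 is 0.13, 0.23 and 0.37. Multiplied by 0.138 this gives about 0.018, 0.031 and 0.050; multiplied by 0.031, about 0.004, 0.007 and 0.011. These are upper bounds for a single exit, because not every exit would be early or disputable.

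**The case against.** The strongest reply is that this is one safety sentence in a condensed article. It does not say that T8 is withheld, and the full protocol may settle follow-up after a stop. That is a fair caution, and the reason to say *read as written*. But the sentence is a stated rule whose object is the study, and nothing in the article qualifies it.

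The second reply is that ending research contact protects the patient. The same section concedes that some questions may upset participants, and T8 asks about hopelessness and depression. This stands as a reason for clinical discretion. It does not support a rule that closes T8 to every such patient, including those who are later stable and willing.

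The third reply is that the outcomes are descriptive and the shift is small. This stands, and it sets the grade of the point.

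A reader might also infer that staff could steer the feasibility result, because an imposed exit can be classed as related or unrelated and "the only person completely blinded to group assignment will be the data analyst/statistician". The documents do not support making that a specific fault of the harm-risk rule. The relatedness judgement arises for every early exit under Outcomes, the open-label design is declared and its limits are acknowledged, reasons for dropout are tracked, and an exit that does not meet the replacement rule stays among the 15 by default.

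**Conclusion.** A minor point that holds. As worded, a harm-risk stop before T8 removes two secondary outcomes and the exploratory pre/post scores for reasons connected with those outcomes. The size is about 0.07 to 0.13 SD in an arm mean per missing patient, under the assumed 1 to 2 SD difference. That these patients do worse is itself an assumption, though a reasonable one. There is no effect if no such exit occurs.

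Two stronger conclusions should not be drawn. The chances of 0.145, 0.138 and 0.031 are not the risk that the progression decision goes wrong: they are conditional on a disputable exit for which no rate is documented. Nor does it follow that every such exit should count as a non-completion. A crisis brought on by cancer progression would then count against the interpreting mode, while a death from progression would be replaced, which contradicts the principle in Outcomes.

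**What to change.** Reword the sentence in Adverse reactions and events so that risk of harm ends or pauses the counselling sessions, at the clinicians' discretion, but does not by itself end data collection. Offer T8 where it is clinically appropriate and the patient is willing. Tabulate these exits by arm, with the number of sessions attended.

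Leave the relatedness rule in Outcomes as it is. If such an exit occurs before five sessions, show the 11-of-15 result twice, once with the patient replaced and once counted as a non-completion. An arm with 10 completers, 4 non-completers and one such exit would then be seen openly as yellow in one reading and green in the other, if the replacement completes. The attendance logs already hold what is needed.

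Cost: no new instrument or visit, since T8 already exists. The change needs an IRB-approved amendment while the trial is enrolling (since March 2024), and clinical judgement on whether and when to re-contact a patient who has been at risk.

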**Methods:**

A total of 45 participants will be randomly assigned to one of 3 arms (*n* = 15 RCMI, *n* = 15 RSMI, and *n* = 15 bilingual provider) to receive 6 counseling/psychotherapy sessions. Feasibility and acceptability of the interpreting modalities (RCMI, RSMI) will be evaluated through self-report assessments. Secondary outcomes will include therapeutic alliance, MCP-Ch content comprehension, and clinically significant interpreting errors across the interpreting (RCMI, RSMI) arms. Semi-structured interviews with a purposively sampled subset of patients, their interventionists, and interpreters (if applicable) across all 3 arms will assess potential barriers and facilitators to successful interpreter-mediated communication and outcomes.

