### Trial design

INTERPRET-PSY is a mixed method, explanatory sequential (QUANT qual), 3-arm pilot randomized controlled trial (RCT) being conducted in preparation for a subsequent, fully powered RCT evaluating the efficacy of interpreting methods to deliver psycho-oncology care. A timeline of the INTERPRET-PSY project is presented in Fig. 2. This open-label, parallel-group RCT aims to enroll 45 Mandarin-speaking patients with LEP. Participants will be registered by the Memorial Sloan Kettering Cancer Center (MSK) institution-wide, central Protocol Participant Registration system and randomized (using the Clinical Research Database) with equal probability to the RSMI, RCMI, or bilingual provider group and will complete self-report measures (*n* = 15 in each group). As this is a pilot study and not a fully powered RCT, the sample size was determined based on resource considerations and a sample size calculation for the primary outcome of RSMI/RCMI feasibility (see Data analysis plan below) [29]. A purposively sampled subset of participants (i.e., high- and non-responders) in each arm (*n*~6 per arm, pending saturation) and their interpreters and interventionists will be followed up for qualitative data collection in semi-structured interviews to contextualize outcomes and identify barriers and facilitators to interpreter-mediated psycho-oncology counseling.

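### The serious adverse event definition requires that the study caused the harm, so serious events judged unrelated leave the count, and any by-arm summary rests on attribution with no blinded assessor described

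*Protocol article*

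**What the plan says.** The section Adverse reactions and events of the protocol article fixes the definition for this study: "a serious adverse event is defined as an event that, as a direct result of the study, causes serious harm", with death and serious injury as examples. No definition free of causality appears elsewhere in the article.

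The same section sets two reporting routes. For the ethics board: "The principal investigators will report unanticipated and serious adverse events to the IRB in a timely manner on an ongoing basis". For the funder: "Adverse events are also reported as part of the progress reports submitted to the National Institutes of Health".

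On masking, Trial design says "This open-label, parallel-group RCT aims to enroll 45 Mandarin-speaking patients with LEP", and Assignment of interventions says that "the only person completely blinded to group assignment will be the data analyst/statistician". That section also says that a principal investigator "will be conducting supervision for the interventionists". Eligibility criteria restricts entry to stage III or IV disease or a rough equivalent. Outcomes names cancer progression and death as examples of reasons for dropout that are unrelated to the intervention.

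**The concern.** Seriousness describes what happened to the participant. Relatedness is an opinion about why it happened. Safety records normally keep the two apart, so that the first can be counted without depending on the second. Here an event must pass the causal test before it can be called serious.

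This matters more than usual in this population. Deaths and other serious events from advanced cancer are foreseeable, and most will probably be put down to the disease. Each one judged unrelated leaves the serious event count. The judgement is made in a trial where, apart from the analyst, no one is described as completely blinded. If staff hold different expectations of the interpreting modes, similar events could be attributed differently by arm. A by-arm serious event summary would then reflect attribution as well as occurrence.

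The pilot is meant to inform a larger trial. A count restricted in this way would be a poor guide to the serious event burden to plan for.

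**Working it through.** No safety figure is stated in the article, so there is nothing to reproduce. The check has two parts: reading the provisions together, and an illustration under assumed rates.

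**Provisions side by side**

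1. Definition: serious harm and direct causation by the study are both required. An event with a serious outcome judged unrelated fails the second condition and is not a serious adverse event.
2. Who judges: the article does not say who classifies causality. It says that the principal investigators report events and that the research team judges whether the intervention is causing harm. Blinded panels are described for coding interpreting errors (Data analysis plan). None is described for event attribution.
3. A similar judgement appears in Outcomes: a participant who drops out before Session 6 for a reason unrelated to the intervention, death included, is non-evaluable and replaced. A death before Session 6 judged unrelated therefore leaves both the serious event count and the feasibility denominator, although its reason is tracked.

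**Illustration**

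Inputs: 45 participants, 15 per arm (article). The all-cause serious event rate p and the share q attributed to the study are not given. I assume p = 10–30% and q = 5–50%.

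Formulas: expected events serious by outcome = 45 × p; expected events counted under the definition = 45 × p × q; chance that none is counted = (1 − p × q)^45.

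| p | Serious by outcome | q | Counted | Chance none counted |
|---|---|---|---|---|
| 10% | 4.5 | 50% | 2.25 | 0.10 |
| 10% | 4.5 | 10% | 0.45 | 0.64 |
| 10% | 4.5 | 5% | 0.225 | 0.80 |
| 20% | 9 | 50% | 4.5 | 0.009 |
| 20% | 9 | 10% | 0.90 | 0.40 |
| 20% | 9 | 5% | 0.45 | 0.64 |
| 30% | 13.5 | 50% | 6.75 | 0.001 |
| 30% | 13.5 | 10% | 1.35 | 0.25 |
| 30% | 13.5 | 5% | 0.675 | 0.51 |

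Example: p = 20%, q = 10% gives p × q = 0.02 and 0.98^45 = 0.40.

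**Differential attribution.** Suppose two arms share the same true rate of 20%, but 10% of events are attributed in one and 50% in the other. Expected counts are 15 × 0.20 × 0.10 = 0.3 and 15 × 0.20 × 0.50 = 1.5. The chance of a zero count is 0.98^15 = 0.74 in the first arm and 0.90^15 = 0.21 in the second. The arms look different although nothing differs except attribution.

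**What complete counting would not give.** With 15 per arm and two-sided 0.05, the normal approximation with pooled null variance gives power of about 27% for 10% versus 30% and 22% for 20% versus 40%. No definition makes this pilot able to test a safety difference.

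**The case against.** The strongest reply is that the serious event label is not the only record of harm, and most of this reply stands.

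- Adverse events go to the funder and unanticipated events to the ethics board, with no causality condition attached in the text.
- Signs of acute risk of harm to self or others go at once to the principal investigators, whatever the cause (Protection of human subjects).
- Dropout reasons are tracked. Change in distress, anxiety and depression, and hopelessness is summarized by arm, which suits a counseling trial whose adverse events are expected to be non-physical.
- Clinically significant interpreting errors in Session 1 are coded by blinded panels, so a missed disclosure in that session could surface without anyone blaming the study.

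A reader might therefore infer too much from the definition. Four stronger readings are not supported:

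- That harm cannot be compared between arms. The records just listed contradict it.
- That the monitoring committee could not compare arms. The article does not say what the committee receives; that belongs to a monitoring plan that is not shown.
- That the definition undermines stopping for harm. That provision applies where "the intervention is found to be associated with an undue risk of harm to participants". It is framed in terms of distress, impairment and risk of harm, and does not mention serious adverse events.
- That a supervising investigator makes the attribution. The supervision sentence explains why blinding is limited, not how events are classified.

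It is also fair that by-arm safety tables and recording fields are commonly left to the full protocol, so their absence from an article is no finding.

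What the reply does not remove is the stated rule. The other records do not add up to a complete serious event count. A death from advanced cancer may well not be called unanticipated. Dropout reasons are not described as safety data. A participant who dies before the post-intervention assessment has no change score. The error coding stops after Session 1.

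**Conclusion.** The point holds in a limited form. As written, the definition merges seriousness with causality, so the serious adverse event count is incomplete by design and depends on attribution for which no blinded assessor is described. Any by-arm summary of that count is open to differential attribution.

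Its size cannot be taken from the document. Under the assumed rates the chance of counting no serious event among 45 runs from 0.001 to 0.80, depending mainly on the share attributed. It would be tempting to say that the count is near zero by construction. That is not shown, because at an attributed share of 50% a zero count is unlikely.

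Severity is minor to moderate. The primary outcome, progression criteria, sample size and error rates are unaffected, and the text plans no between-arm safety test. The case for change is complete and unbiased recording in a pilot meant to inform a definitive trial.

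**What to change.** Define a serious adverse event by the outcome of the event, regardless of cause. Record relatedness to the study as a separate field. List all serious events descriptively by arm, with relatedness shown beside each. Expedited reporting to the ethics board can stay limited to related or unanticipated events under local policy.

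The cost is one reworded definition, one field per event, and slightly more recording of cancer-related events. No between-arm test should be added.
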